## Abstract

**Introduction::**

Several studies have found that obesity is associated with atopic dermatitis (AD); however, the mechanisms underlying the association are largely unknown. This study aims to assess the association of AD with obesity in the Korean population and verify its mechanism via a multi-omics analysis.

**Methods and analysis::**

A case–control study will be conducted in the Republic of Korea. A total of 80 subjects, aged 4 to 12 years, matched for age and sex, with body mass index at or above the 85th percentile or at or below the 25th percentile, will be included. Subjects will be assigned to the following 4 groups: obese/overweight with AD, normal/underweight with AD, obese/overweight control, and normal/underweight control. Serum metabolome and immune biomarkers, as well as fecal metabolome and microbiome biomarkers, will be analyzed. Serum eosinophil cationic protein, total serum Immunoglobulin E (IgE), and specific IgE will be analyzed to assess allergic tendency. The SCORing of AD index, the children's dermatology life quality index, body composition analysis, and the Korean gastrointestinal symptom rating scale will be obtained to assess the disease status and severity of the subjects.

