### Study design and procedure

2.2

This case-control study will be conducted at Wonkwang University Iksan Korean Medicine Hospital in the Republic of Korea. The study has 4 arms: an obese/overweight with AD group, a normal/underweight with AD group, an obese/overweight control group, and a normal/underweight control group. Twenty subjects will be assigned to each arm and a total of 80 subjects will be recruited for this study.

After potential participants voluntarily consent to the study, they will be screened using predetermined inclusion/exclusion criteria at the first visit. To be assigned to a group, subjects will be evaluated based on demographic characteristics, medical history, and physical examination including Hanifin & Rajka AD criteria. The SCORing of AD (SCORAD) index, the Children's Dermatology Life Quality Index (CDLQI), and the Korean Gastrointestinal Symptom Rating Scale (KGSRS); body composition analysis will also be performed to confirm the subjects’ general health and disease status.

The 3-day controlled meal will be provided to the subjects in order to reduce microbial changes due to variable food intake. The 3-day meal is prepared in an allergy-free manufacturing facility and is free of eggs, milk, soy, and wheat, which are known to be the main causes of food allergies.

After the 3-day meal, SCORAD index, CDLQI, KGSRS, and body composition analysis will be evaluated. Blood and fecal samples will be obtained after the controlled meal in order to analyze microbiome-metabolome-immune biomarkers. A fecal sample will also be obtained before the controlled meal in order to assess the microbial differences between the experimental groups before and after the controlled meal. The detailed design is summarized in Figure 1.

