### Participants

2.3

Participants defined as having AD are those who satisfy the Hanifin & Rajka AD criteria. Non-AD subjects are those who do not satisfy the Hanifin & Rajka AD criteria and not have asthma, allergic rhinitis, allergic conjunctivitis, or food allergies.

The obese/overweight subjects are those with a body mass index (BMI) at or above the 85th percentile, matched for age and sex. The normal/underweight patients have a BMI at or below the 25th percentile, matched for age and sex. BMI percentile in the same age and sex group is decided based on the World Health Organization (WHO) Child Growth Standards proposed in 2007.

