### Statistical plan

2.5

The participants’ characteristics will be summarized using means and standard deviations for continuous variables that satisfy normality or using median and interquartile range for non-normal data. Group differences will be assessed using 1-way analysis of variance (ANOVA) or the Kruskal–Wallis test. In addition, the independent-samples t-test or chi-squared test will be used to analyze differences between the AD and non-AD groups, as well as between the obese and non-obese groups.

The microbiome sequencing data obtained from feces will be analyzed using the Quantitative Insights into Microbial Ecology (QIIME) and assigned to an operational taxonomic units (OTU) table generated using the EzTaxon database. The Phylogenic Investigation of Communities by Reconstruction of Unobserved States (PICRUSt) program will be used to compare differences in gene expression. Alpha diversity metrics include the number of OTUs (species richness), the Simpson or Shannon diversity indices, and the Chao1 metric. Beta diversity will be analyzed using both unweighted and weighted UniFrac distances.

Metabolome data will be analyzed using univariate statistics and multivariate modeling. All analyses will be implemented in R statistical programming. Statistical differences among groups will be independently evaluated for known and unknown metabolites, and cluster analysis will be used to compare the metabolites profiles. Metabolites displaying significantly altered delta values (*P* <.05) will be used for principal components analysis (unsupervised) and orthogonal partial least squares analysis (supervised) projection to latent structures.

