## Discussion

3

This is a study protocol to investigate the association of AD with obesity in the Korean population and verify its mechanism by analyzing gut microbiome–metabolome–immune biomarkers using a multi-omics approach.

In this study, we included 4 to 12-year-old children as subjects for several reasons. First, AD is one of the most common chronic childhood skin diseases, affecting up to 15% to 20% of children worldwide.^[16,17]^ Given that the symptoms of AD usually begin in infancy, the majority of AD cases develop before the age of 5 years,^[18,19]^ and the prevalence in teenagers seems to be falling significantly,^[20]^ children aged 4 to 12 have a high prevalence of AD. Second, most children aged 4 to 12 years in Korea, spend most of their time in a group setting, such as a kindergarten or school, eating a similar Korean-style diet consisting of rice, soup, and side dishes. Third, it is known that the phylogenetic composition of bacterial communities evolves towards an adult-like composition within 3 years after birth.^[21]^

In the present study, a 3-day controlled diet will be provided to ensure better dietary control, and fecal samples will be collected both before and after controlled meals. It is now understood that diet plays a significant role in shaping the microbiome, with experiments showing that dietary alterations can induce large, temporary microbial shifts within 24 hours.^[22,23]^ Because there is no appropriate guideline in terms of dietary control in microbiome analysis, we assumed that 3-day-controlled meal is sufficient to eliminate effects of diet. We also will analyze microbial changes before and after the 3-day meal to confirm whether the 3-day controlled meal is sufficient to remove microbial changes due to diet.

This study protocol represents a unique opportunity to enhance our understanding of the association between AD and obesity in terms of gut microbiome, metabolome, and immunological mechanisms and may, therefore, serve to improve future management strategies for AD.

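### The abstract calls the 80 subjects age- and sex-matched, but the Methods match only the BMI percentile, and the group tests named adjust for neither age nor sex

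*Protocol article*

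**What the plan says.** The abstract (Methods and analysis) attaches the matching to the children: "A total of 80 subjects, aged 4 to 12 years, matched for age and sex".

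Section 2.3 (Participants) uses the same words for the BMI cut-offs: "The obese/overweight subjects are those with a body mass index (BMI) at or above the 85th percentile, matched for age and sex", and "The normal/underweight patients have a BMI at or below the 25th percentile, matched for age and sex". The sentence that follows explains the phrase: "BMI percentile in the same age and sex group is decided based on the World Health Organization (WHO) Child Growth Standards proposed in 2007". Inclusion criterion 2 in section 2.3.1 likewise ties it to the WHO standard.

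On forming the arms, section 2.2 says "To be assigned to a group, subjects will be evaluated based on demographic characteristics, medical history, and physical examination including Hanifin & Rajka AD criteria". It gives 20 children per arm and 80 in total. Section 2.3.3 describes recruitment by advertisement.

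Section 2.5 (Statistical plan) names one-way ANOVA or Kruskal–Wallis for the four groups. For AD versus non-AD and for obese versus non-obese, "the independent-samples t-test or chi-squared test will be used". Metabolome data get univariate statistics and multivariate modelling, the latter set out as principal components and orthogonal partial least squares. Age and sex do not appear in the section.

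**The concern.** A reader of the abstract would take this to be a matched case–control study. The Methods describe something else: a child's BMI is read against the reference for that child's age and sex. This settles who counts as obese/overweight or normal/underweight. It does not make the four arms alike in age or sex, and it does not standardise IgE, cytokines, metabolites or body composition for age.

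The arms are formed by characteristics the children already have, over an age range of 4 to 12 years, so nothing in the described design protects against the arms differing systematically in age or sex. Since the named tests carry neither variable, such a difference would be read as an effect of AD or of obesity on any marker that changes with age or differs by sex. The AD and obesity contrasts are what the study is for.

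**Working it through.** **Step 1. Where the phrase is attached.**

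| Place | What is said to be matched |
|---|---|
| Abstract | The 80 subjects |
| 2.3 Participants | The BMI percentile, within the same age and sex group of the WHO standard |
| 2.3.1 Inclusion criterion 2 | The BMI percentile, by the WHO standard |
| 2.2 Group assignment | No matching step, ratio, age band or sex quota |
| 2.3.3 Recruitment | No matching step |

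The abstract and the Methods therefore disagree. The demographic evaluation in 2.2 is not a matching rule.

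**Step 2. What the named tests do on each reading.**

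- Children not matched: the unadjusted tests leave any systematic age or sex difference in the estimate.
- Arms frequency-matched: age and sex are balanced. Unadjusted comparisons of continuous markers are then not confounded by them, but lose precision and tend to be conservative.

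**Step 3. Size, as illustration.** The document gives the arm sizes (4 × 20 = 80, which agrees with its total) and the age range. It gives no age distribution by arm and no marker–age correlation. The following are assumptions:

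- age uniform over 4 to 12 completed years, a span of 9 years: SD = 9/√12 = 2.60 years;
- within-group marker–age correlation r of 0.3 to 0.5;
- a systematic mean-age gap of 0, 1 or 2 years;
- no true group effect, and a two-sided 5% t-test of 40 vs 40 (78 df).

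Spurious difference in marker SDs = r × gap / 2.60. Its standard error is √(2/40) = 0.224. Non-centrality = spurious difference / 0.224. The rejection rate comes from the non-central t distribution.

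| Gap (years) | r | Spurious difference (SD) | Non-centrality | False-positive rate |
|---|---|---|---|---|
| 0 | any | 0 | 0 | 5% |
| 1 | 0.3 | 0.115 | 0.52 | 8.0% |
| 1 | 0.5 | 0.192 | 0.86 | 13.6% |
| 2 | 0.3 | 0.231 | 1.03 | 17.5% |
| 2 | 0.5 | 0.385 | 1.72 | 39.8% |

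For 20 vs 20 (38 df) the same inputs give 6.5–9.1% at 1 year and 11–22% at 2 years. If the age span is taken as 8 years (SD 8/√12 = 2.31), the 40 vs 40 figures are 8.8–16% and 21–48%.

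**Step 4. Precision.** With no gap, adjusting for age removes a share r² of the marker variance. The equivalent gain in sample size is 1/(1 − r²) − 1, which is 10% at r = 0.3 and 33% at r = 0.5.

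**The case against.** **The full protocol or analysis plan may settle this.** Matching details and covariate lists are often left to documents not shown here. That is fair, and their absence from an article is not itself the point. What stands is that two statements within the article disagree, and that the tests it does name are unadjusted. It is also fair that the ANOVA and t-test sentences sit in the paragraph that opens with participants' characteristics, so reading them as the final model for every marker is an interpretation. Still, they are the only group-difference tests the section names, and the metabolome paragraph adds univariate statistics without a covariate.

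**The AD arms may be expected to be younger.** A reader might infer this from the Discussion, which says that most AD begins before age 5 and that "the prevalence in teenagers seems to be falling significantly". The text does not support it. The first statement is about age at onset, not age at enrolment, and the second concerns an age band essentially outside the eligible range. The Discussion concludes that prevalence is high from 4 to 12 and gives no gradient within that range. Nothing is said about age in obese versus lean children either.

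**Small arms will differ in age by chance.** They will: the standard error of the mean-age gap is 2.60 × √(2/20) = 0.82 years for 20 vs 20. But a 5% test already allows for chance imbalance. Only a systematic gap inflates its error rate.

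**The age range is defended.** The Discussion cites a similar diet and a gut community that is adult-like by about 3 years of age. This partly answers the point for the microbiome. It does not cover IgE, cytokines, serum metabolites or body composition.

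**Conclusion.** The concern holds in a limited form. What is firm is that the abstract's matching statement conflicts with sections 2.3 and 2.3.1, that the article describes no matching of children, and that the group comparisons it names use neither age nor sex. Confounding by age or sex is therefore a risk left open, not a demonstrated bias, and its direction and size are unknown.

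The 8–14% and 17–40% false-positive rates rest on the assumed systematic gaps of 1 and 2 years, the assumed correlations, and an age SD of 2.6 years. They do not apply if there is no systematic gap or if the arms are frequency-matched; the cost is then lost precision only. The change is worth making on either reading, because adjustment removes the risk in one case and recovers precision in the other.

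**What to change.** 1. **Abstract.** Reword so that age and sex qualify the BMI percentile, as in section 2.3. If matching of children is intended, say so in 2.2 or 2.3 as frequency matching by sex and age band.
2. **Section 2.5.** Replace the unadjusted marker comparisons with linear models that include group, age (continuous) and sex, using transformed or rank-based versions where normality fails. Do this whether or not the arms are frequency-matched.
3. **Microbiome and metabolome.** Carry the same two covariates into any model-based comparison of these data.

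The cost is wording and about two residual degrees of freedom: 80 − 4 = 76 in the four-group model becomes 74. Age and sex are already needed to assign the BMI percentile, so no new data and no further children are required.

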**Discussion::**

The findings of this study are expected to provide evidence of an association between AD and obesity via a gut microbiome-metabolome-immune mechanism. Therefore, it may improve future management strategies for AD.

**Trial registration::**

This study has been registered at the Korean National Clinical Trial Registry, Clinical Research Information Service (KCT0003630).

## Introduction

1

Atopic dermatitis (AD), also known as atopic eczema, is a common chronic inflammatory skin disease characterized by extensive pruritus, a clinical course of symptomatic flares and recurrent eczematous lesions.^[1]^ The pathophysiology of AD is complex and multifactorial, involving epidermal barrier disruption, skin inflammation due to dysregulation of immune responses, immunoglobulin E (IgE)-mediated hypersensitivity, and environmental factors.^[2]^ Although the direct cause and pathophysiology of AD have not been clearly elucidated, several studies have suggested that obesity is associated with AD. Recent systematic reviews found that being overweight or obese was associated with increased prevalence and risk of AD.^[3–5]^ Moreover, levels of serum leptin, a polypeptide hormone produced by adipocytes that helps regulate energy balance by inhibiting hunger,^[6]^ decreased as AD became severe.^[7]^ However, the mechanisms underlying this association are largely unknown.

The gut microbiome has attracted much attention beyond classical infectious diseases. Numerous studies have reported changes in the gut microbiota, not only in gastrointestinal disease but also in obesity and allergic diseases.^[8,9]^ Recent studies have indicated that dysbiosis in *Faecalibacterium prausnitzii* and dysregulation of gut epithelial inflammation might affect the chronic progression of AD by resulting in impairment of the gut epithelial barrier.^[10]^ Alterations in the proportions of *Bacteroidetes* and *Firmicutes*—which account for the majority of gut microbiota—lead to obesity, associated with relatively low gut microbial diversity.^[11,12]^

Based on these previous studies, we hypothesize that the gut microbiome is involved in the mechanism of AD and obesity. This study aims to assess the association between obesity and AD in the context of gut microbiome by analyzing the gut microbiome, the metabolome, and immune biomarkers.

## Methods

2

### Objectives

2.1

The aim of this study is to assess the association of AD with obesity in the Korean population and verify its mechanism by analyzing gut microbiome–metabolome–immune biomarkers using a multi-omics approach.

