#### Inclusion criteria

2.3.1

1.Boys or girls aged 4 to 12 years old.2.BMI at or above the 85th percentile, or at or below the 25th percentile, matched for age and sex based on the WHO Child Growth Standards proposed in 2007.3.Subjects who can follow the dietary guidelines for 3 days.4.Subjects who agree to participate and voluntarily sign a written informed consent form from the legal representatives and/or participants.

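### The AD–obesity association is a stated aim, but recruitment quotas on both AD and BMI class mean the enrolled sample cannot estimate it

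*Protocol article*

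**What the plan says.** The formal aim, in Section 2.1 (Objectives) of the protocol article, has two parts: "The aim of this study is to assess the association of AD with obesity in the Korean population and verify its mechanism". It goes on to name multi-omics biomarker analysis as the means. The Abstract (Introduction) and the opening of Section 3 (Discussion) give the same two-part aim. The Abstract (Discussion) then anticipates the result: "The findings of this study are expected to provide evidence of an association between AD and obesity via a gut microbiome-metabolome-immune mechanism".

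Section 2.2 labels the study case-control and lists four arms: "an obese/overweight with AD group, a normal/underweight with AD group, an obese/overweight control group, and a normal/underweight control group". It continues: "Twenty subjects will be assigned to each arm and a total of 80 subjects will be recruited for this study". Children enter a group according to their own status: "To be assigned to a group, subjects will be evaluated based on demographic characteristics, medical history, and physical examination including Hanifin & Rajka AD criteria". BMI eligibility in Section 2.3.1 is "BMI at or above the 85th percentile, or at or below the 25th percentile, matched for age and sex".

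Section 2.5 plans one-way ANOVA or Kruskal–Wallis tests across groups. It adds that "the independent-samples t-test or chi-squared test will be used to analyze differences between the AD and non-AD groups", and plans the same for obese versus non-obese children. It describes no sampling fractions or reweighting.

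The last paragraph of Section 1 gives a narrower aim, which places the AD–obesity link within the setting of the gut microbiome.

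**The concern.** A case-control study can estimate an odds ratio because exposure is left free within cases and within controls. Here the exposure, BMI class, is also set by recruitment: half of the children with AD and half of the controls will be obese or overweight because the plan says so. The first part of the stated aim therefore has no estimator in the enrolled data.

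What is at stake is the permitted conclusion. The objective and the Abstract prepare readers for evidence on whether AD and obesity are associated. The study can describe how biomarkers differ between children already classified on both conditions. It cannot say whether the conditions go together more often than chance, and biomarker findings could be misread as if it had.

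**Working it through.** **Inputs.** Four groups and 20 children per group (Section 2.2). No effect size, SD or power assumption is needed for the main result.

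**Plan's own figure.** 4 × 20 = 80, which matches the stated total.

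**Odds ratio in the enrolled sample.**

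| | Obese/overweight | Normal/underweight |
|---|---|---|
| AD | 20 | 20 |
| Control | 20 | 20 |

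OR = (20 × 20)/(20 × 20) = 1.00, and chi-squared = 0.

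**Why the truth drops out.** Let π be the population share of a cell and f the fraction of that cell that is enrolled, with the first index for AD and the second for obesity. Then

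enrolled OR = population OR × (f₁₁ f₀₀)/(f₁₀ f₀₁).

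- In an ordinary case-control study f depends on AD only. The second factor is 1 and the population OR survives.
- With a quota of 20 in every cell, f is proportional to 20/π. The second factor is then (π₁₀ π₀₁)/(π₁₁ π₀₀), the reciprocal of the population OR, and the product is 1.

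**Simulation check.** Quotas were filled from populations with assumed ORs of 0.5, 1, 1.5, 2 and 3. The assumed AD prevalence was 15% in the lower BMI class, and the assumed obese/overweight share among eligible children was 0.15/(0.15 + 0.25) = 0.375. The enrolled OR was 1.00 every time.

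**Dropout.** Section 2.6 allows discontinuation. If two obese children with AD were lost and not replaced, OR = (18 × 20)/(20 × 20) = 0.90. That reflects who left, not the association in the population.

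**What remains estimable.** Detectable differences at 80% power, two-sided 0.05, normal approximation, with (1.960 + 0.842) = 2.802:

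- AD versus control, or obese versus non-obese, 40 versus 40: 2.802 × √(2/40) = 0.63 SD.
- SCORAD by BMI class among children with AD, 20 versus 20: 2.802 × √(2/20) = 0.89 SD.
- AD × BMI-class interaction (a difference of differences over four cells of 20): 2.802 × √(4/20) = 2.802 × 0.447 = 1.25 SD.

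**The case against.** The strongest reply is that the aim is mechanistic. Section 1 takes the AD–obesity link from systematic reviews, says that the mechanism is unknown, and places the aim within the gut microbiome. Section 2.1 goes on to biomarker analysis as its means, and the Abstract's expected conclusion speaks of an association acting through a mechanism. A balanced 2 × 2 quota design suits that purpose, and the biomarker comparisons in Section 2.5 are unaffected. This softens the contradiction but does not remove it: the formal objective joins the population association to the mechanism as an aim in its own right, and the Abstract and Section 3 repeat it.

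Some stronger readings are tempting but are not supported:

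- A reader might infer that the study will report an odds ratio of 1 or a null chi-squared test for AD by obesity. Section 2.5 names no such table or odds ratio. The value of 1 shows that the association is not estimable; it is not a forecast of a reported result. A confidence interval around a quota-fixed quantity would mean nothing.
- A reader might blame the omitted middle range of BMI. That changes the contrast to extreme groups but does not by itself prevent an odds ratio.
- A reader might blame the single blood draw for the mechanism being unverifiable. A second draw around a three-day meal would not verify it either. The limit is the observational design, and feces are sampled twice.
- A reader might describe the sample as drawn only from one hospital. The site is one hospital, but Section 2.3.3 also advertises in the community.
- A reader might conclude that population margins do not exist. The article is only silent on them. The point here is confined to what the enrolled sample can show.

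**Conclusion.** The objective is wrong as written. The marginal AD–obesity association cannot be estimated from the 80 enrolled children, and no analysis described in Section 2.5 could recover it. The enrolled odds ratio is exactly 1 if all quotas are filled and kept, and any departure is an artefact. This rests only on the fixed group sizes in Section 2.2. The power figures additionally assume two-sided 0.05, 80% power and a normal approximation.

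The finding goes no further. Sample size, eligibility and the planned biomarker comparisons stand. A reader might infer that the whole study is uninformative about AD and obesity, but contrasts by AD, by BMI class, and of severity by BMI class within AD remain valid targets.

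**What to change.** 1. In the Abstract (Introduction), Section 2.1 and Section 3, delete the claim to assess the AD–obesity association in the Korean population. Use the narrower aim of Section 1, for example: *to explore differences in gut microbiome, metabolome and immune markers across four groups of children defined by AD status and BMI class*.
2. Change *verify* to *explore* wherever the mechanism is named, because the study is observational.
3. Align the expected conclusion in the Abstract (Discussion) with that aim.
4. Add to Section 2.2 or 2.5: *The numbers of children by AD status and BMI class are fixed by design and give no evidence on whether AD and obesity are associated.*
5. Only if an AD × BMI-class interaction is named as an aim: add a two-way model with that term to Section 2.5, since one-way and two-group tests do not test it. Label it exploratory, given the roughly 1.25 SD needed.

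Steps 1 to 4 need no new children, samples or data. Step 5 adds one analysis. The downside is a narrower claim.

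Keeping the association as an aim would mean leaving BMI class free within children with AD and controls, and 80 children would be too few for a moderate association. With 40 versus 40 and an assumed obese/overweight share of 0.25 to 0.50 among controls, power is about 30% to 33% at an assumed OR of 2, and 80% power needs about 134 to 152 per group. Rewording is the proportionate choice.

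### The objective promises to verify a mechanism, but every marker is sampled after AD and BMI class are established, so only cross-sectional association can be shown

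*Protocol article*

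**What the plan says.** The formal objective (section 2.1) is to study the AD–obesity association "and verify its mechanism by analyzing gut" and related markers. The Introduction of the Abstract and the opening of the Discussion (section 3) state the same aim. The Abstract's Discussion adds that the findings are "expected to provide evidence of an association between AD and obesity via a gut microbiome-metabolome-immune mechanism".

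The Introduction (section 1) is more cautious. It hypothesises that the gut microbiome is involved, and it aims to look at the AD–obesity association in that context.

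On design, section 2.2 says: "This case-control study will be conducted at Wonkwang University Iksan Korean Medicine Hospital". Children are put into four arms by AD status and BMI class, and "Twenty subjects will be assigned to each arm and a total of 80 subjects will be recruited for this study". Section 2.3 defines the cases: "Participants defined as having AD are those who satisfy the Hanifin & Rajka AD criteria". BMI class is fixed at entry by percentile.

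On timing, section 2.2 says: "Blood and fecal samples will be obtained after the controlled meal". One further stool sample is taken before the meal. The Discussion explains that the stool pair is there to check whether three days of controlled diet are enough. It also notes that "the majority of AD cases develop before the age of 5 years", while enrolment covers ages 4 to 12.

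**The concern.** To verify a mechanism, and to say that an association runs *via* a chain of markers, is to claim a causal order: obesity changes the gut, the change alters metabolites and immune signals, and these lead to AD. To support that order, a study needs something that places the marker before the disease, such as samples taken before onset, follow-up of unaffected children, or an intervention that changes the microbiome in some groups and not in others. The article describes none of these.

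What is at stake is the conclusion. If the four arms differ in the hoped-for way, a reader who holds the result against the objective as written would take the mechanism as verified. The same data would fit equally well if the marker pattern were a consequence of long-standing AD and of excess weight.

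**Working it through.** **Step 1: order of events, from the article.**

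| Item | When | Source |
|---|---|---|
| AD status by diagnostic criteria | First visit, before assignment to an arm | 2.2, 2.3 |
| BMI class | At entry | 2.3, 2.3.1 |
| First stool | Before the 3-day meal | 2.2 |
| Serum (once) and second stool | After the 3-day meal | 2.2 |

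Every marker sample comes from a child whose AD and BMI class are already present. On the Discussion's own statement about age at onset, in most cases AD will have begun before age 5, so for older children the samples will often follow onset by years. The only repeated marker sample spans the meal. All four arms receive that meal, so a before/after change carries information about diet and none about the onset of AD or obesity.

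**Step 2: what the sampling scheme observes.** The arm sizes reproduce: 4 × 20 = 80. Because AD and BMI class are set by recruitment at 20 per arm, the informative quantity is the distribution of the markers M given obesity O and AD, P(M | O, AD).

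**Step 3: can that quantity separate the two directions?** The values below are assumed for illustration and are not in the document. Take a binary marker.

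*Marker before AD.* P(M) = 0.3 in lean and 0.6 in obese children; P(AD) = 0.10 without and 0.25 with the marker.

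- Lean: P(AD) = 0.3 × 0.25 + 0.7 × 0.10 = 0.075 + 0.070 = 0.145
- Obese: P(AD) = 0.6 × 0.25 + 0.4 × 0.10 = 0.150 + 0.040 = 0.190

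By Bayes' rule, P(M | O, AD) is:

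- Lean, no AD: 0.3 × 0.75 / 0.855 = 0.263
- Lean, AD: 0.075 / 0.145 = 0.517
- Obese, no AD: 0.6 × 0.75 / 0.810 = 0.556
- Obese, AD: 0.150 / 0.190 = 0.789

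*AD before marker.* Let AD occur in 0.145 of lean and 0.190 of obese children by some other route, and let the marker then appear with the four probabilities just listed. Joint probabilities with AD present are:

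| | Marker first | AD first |
|---|---|---|
| Lean, marker absent | 0.7 × 0.10 = 0.070 | 0.145 × 0.483 = 0.070 |
| Lean, marker present | 0.3 × 0.25 = 0.075 | 0.145 × 0.517 = 0.075 |
| Obese, marker absent | 0.4 × 0.10 = 0.040 | 0.190 × 0.211 = 0.040 |
| Obese, marker present | 0.6 × 0.25 = 0.150 | 0.190 × 0.789 = 0.150 |

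The two models agree in every cell. With 20 children per arm, both predict on average 5.3, 10.3, 11.1 and 15.8 marker-positive children (20 × 0.263, 0.517, 0.556 and 0.789).

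**Step 4: does this depend on the chosen values?** No. The identity P(M | O) × P(AD | M) = P(AD | O) × P(M | O, AD) holds for any chain in which O acts on AD only through M. M may also stand for the whole linked panel of microbial, metabolic and immune markers. More children reduce the error around the four arm values but do not separate the models, and neither does integrating the layers.

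**The case against.** The strongest reply is that the article calls itself a case–control study openly. Inability to order marker and disease is inherent in such a study of prevalent cases, and no sample, group or test would change under the fix. What remains is an over-strong verb. The Introduction's wording is softer, the Abstract speaks of evidence rather than proof, and the remarks on management are conditional.

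Part of this stands. The design is legitimate for describing marker patterns, and the Introduction's aim is attainable for that purpose. But disclosing the design does not make the stated objective attainable. The verb in section 2.1 is unhedged and appears in three places, and the softer sentence does not withdraw it.

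A statistical analysis plan that is not shown cannot rescue the claim either, because no analysis of these samples recovers direction. The objection is to what the article states, not to something it leaves out.

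A reader might go further and infer that the plan will produce false mediation findings at some calculable rate. The document does not support that: section 2.5 lists group comparisons, diversity measures and multivariate profiling, and plans no path or mediation model to which an error rate could attach. Nor do the management sentences need deleting, since both say only that the work may help.

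**Conclusion.** The point holds for the objective and for the word *via*. The objective claims a property the design does not have: the data can show which markers differ by AD, BMI class and their combination, and can be consistent with a mechanism, but cannot verify it or its direction. This is a matter of identification, so it has no size that a sample-size change would reduce. In the illustration the two explanations differ by exactly zero in all four arms.

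The conclusion rests on the timing stated in sections 2.2 and 2.3, and on the article describing no sample before onset, no follow-up beyond the meal and no intervention on the microbiome that differs between arms. The marker and AD probabilities are assumed, but the conclusion does not depend on them. It would be too strong to read this as saying that the study has no value or that none of its aims can be met; the exploratory aim in the Introduction shows otherwise.

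**What to change.** - In the Abstract's Introduction, section 2.1 and the opening of the Discussion, replace the promise to verify the mechanism with: *identify gut microbiome, metabolome and immune markers associated cross-sectionally with AD, BMI class and their combination*. This brings the objective into line with the Introduction.
- In the Abstract's Discussion, replace the *via* wording so that the expected evidence is *consistent with, but not establishing,* such a mechanism.
- Add one sentence limiting the conclusion: direction between markers and disease is not identified because cases are prevalent.

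No extra model is needed, since models fitted in each direction would not reveal which is true. The conditional management sentences can stay. The change needs no new children, samples or time; the downside is a more modest stated claim.
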